### Participants and recruitment

Participants will be employees reporting high levels of work-related fatigue. Every employee – regardless job position – can sign up for participation. Participants will be recruited through advertisements with study information in personnel magazines, on facebook pages, and on intranet of large organizations in the region(s) in which the intervention will be carried out. Furthermore, advertisements and news items will be placed in (local) newspapers and on social media.

Inclusion criteria will be based on existing cut-off scores on two validated measures of work-related fatigue: a) ≥2.2 on the emotional exhaustion scale of the Dutch version of the Maslach Burnout Inventory [49]; b) ≥22 on the Fatigue Assessment Scale [50]. Participants can fill out these two scales on the study website (www.runtervention.nl). When participants score high on both scales, the researcher ([name]) will ask these participants for further information about exclusion criteria by email. Exclusion criteria will be: a) ≥ one hour exercising a week; b) fatigue attributable to a medical condition; c) currently or in the past six months receiving psychological and/or pharmacological treatment; d) drug dependence; e) contraindications to exercise. Contraindications to exercise will be measured by the Physical Activity Readiness Questionnaire (PAR-Q; [51]). Eligible participants will be invited for an appointment with the first author ([name]) or research assistants. During this appointment, the baseline measures (T0; except for the two measures of work-related fatigue that are already filled out) will be completed, the cognitive performance tests will be done, and the randomization procedure will be carried out. A separate appointment will be planned for the aerobic fitness test.

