### Randomization and blinding

Participants will be randomly assigned to either an exercise condition or a wait list condition at a 1:1 ratio. Because the intention is to conduct the exercise intervention in groups of 10 participants, randomization will be based on a block size of 20. When the number of 20 eligible participants in a block is reached, participants in the exercise intervention condition start the intervention and the participants in the wait list condition remain on the wait list. The randomization procedure will be carried out after the participant has completed the baseline measurement (T0). The randomization procedure will be executed by the first author ([name]) or research assistant, using sealed opaque envelopes. The participant opens the envelope and tells the researcher to which condition (s)he has been assigned.

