### Analyses of primary and secondary outcomes

We will use intention-to-treat analysis, meaning that all participants who are randomized to a condition will be included in the analyses. To test the efficacy of the exercise intervention (i.e. change in primary and secondary outcomes from pre [T0] to post [T6]), we will perform 2x2 repeated measures (M)ANOVAs with condition (exercise versus wait list) as between-subjects factor, and time (pre [T0] versus post [T6]) as within-subjects factor. We will conduct a RM-MANOVA for the three indicators of work-related fatigue together (*Hypothesis 1*). Furthermore, we will conduct separate RM-(M)ANOVAs for respectively self-efficacy (*Hypothesis 2a and 2b*), sleep (*Hypothesis 2c and 2d*), work ability (*Hypothesis 2e*), cognitive functioning (*Hypothesis 2f*), and aerobic fitness (*Hypothesis 2 g*). The Matching Task will be analyzed using a 2x2x2 mixed design ANOVA, with ‘run type’ (switch versus repetition), and time (pre versus post) as within-subjects factors, and condition as between-subjects factor (exercise versus wait list). In all analyses, we are particularly interested in the ‘condition x time’ interaction, because this indicates that the conditions differ from each other with respect to the development of the outcome measure over time. If applicable, significant interactions will be further examined by paired-sample t-tests. Partial eta-squared will be reported as effect size.

Additionally, to obtain more thorough insight into the clinical meaningfulness of the changes brought about by the exercise intervention [81], we will perform a Chi-Square Test to see if the number of participants who score below cut-off scores of fatigue after the intervention period (T6) differs between the intervention and the control condition (emotional exhaustion <2.2 on the UBOS; overall fatigue: <22 on the FAS).

To investigate whether intervention-effects last during the follow-up period, for each primary and secondary outcome measure, a repeated measures MANOVA will be performed to see whether it differs between pre (T0), post (T6), 6 weeks after the intervention period (T7), and 12 weeks after the intervention period (T8). If the overall time effect of MANOVA is significant, post hoc tests will be carried out to exactly determine between what time points the outcome had changed. As follow-up measures are only available for the intervention condition, the control condition will not be included in these analyses.

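### Falling below the fatigue cut-offs at T6 is compared by a valid but unadjusted chi-square test with no named effect measure; using the T0 score would gain modest precision at no cost

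*Protocol article*

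**What the plan says.** In the protocol article, *Analyses of primary and secondary outcomes*, the main efficacy analyses are repeated measures (M)ANOVAs judged by the condition by time interaction. For these, "Partial eta-squared will be reported as effect size". The next paragraph adds a further comparison, meant "to obtain more thorough insight into the clinical meaningfulness of the changes brought about by the exercise intervention": "we will perform a Chi-Square Test to see if the number of participants who score below cut-off scores" at T6 differs between conditions. The thresholds are "emotional exhaustion <2.2 on the UBOS; overall fatigue: <22 on the FAS". No covariate is named for this comparison, and no risk difference, odds ratio or interval.

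*Participants and recruitment* sets entry at "a) ≥2.2 on the emotional exhaustion scale of the Dutch version of the Maslach Burnout Inventory [49]; b) ≥22 on the Fatigue Assessment Scale". Both conditions must be met before a person goes further ("When participants score high on both scales"). The two scores come from screening, because the T0 appointment covers all baseline measures "except for the two measures of work-related fatigue that are already filled out". They therefore precede randomisation, which is 1:1 (*Randomization and blinding*).

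**The concern.** Every participant starts at or above the threshold that defines the outcome. Someone who enters at 2.2 on emotional exhaustion crosses with a very small change, while someone who enters at 5 must fall by almost 3 points on a 0-6 scale. The starting score is thus a natural prognostic variable for this binary outcome. It is known for everyone before allocation, and the chi-square test does not use it. The other between-arm efficacy analyses in the article do use T0, through the condition by time interaction or through growth models that start at T0.

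The second part is reporting. This is the analysis offered to show clinical meaning, yet only a test is named. Partial eta-squared belongs to the preceding (M)ANOVA paragraph and does not describe a difference between two proportions.

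At stake are the precision and readability of a supportive result, not the validity of the trial's main conclusion.

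**Working it through.** **The plan's own figure.** The article gives no power figure for the cut-off comparison. Its only calculation (*Sample size*) is for the pre-post repeated measures ANOVA: effect .15 (taken as Cohen's f), two-sided 5%, power 80%, correlation .05, N = 90. It matters here because it carries the only pre-post correlation in the article. With λ = f²·N·m/(1−ρ), m = 2 and df 1 and N−2:
- ρ = .05 as printed: λ = 0.0225·90·2/0.95 = 4.26; power 53.3%; N for 80% power is 168.
- ρ = .5: λ = 0.0225·90·2/0.5 = 8.10; power 80.4%; N is exactly 90.

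The value consistent with N = 90 is therefore .5, but .05 is what is printed, so both belong in the range. The mismatch itself is a separate matter.

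**Inputs for the check.** From the article: 90 analysed, 1:1, so 45 per arm; entry at or above the cut-off; T6 outcome below the cut-off. Not in the article and therefore assumed: means, SDs, treatment shift, T6 proportions and normal scores. Selection is modelled on one scale at a time.

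**Model A.** Score with mean 2.9 and SD 1.1, selected at or above 2.2 at T0, shift 0.5 points. At correlations .5 to .8 the proportions below the cut-off are about 11-18% in control and 27-34% with exercise. The uncorrected chi-square test is compared with the likelihood-ratio test for condition in a logistic regression that includes T0. Power (%), chi-square / adjusted, in three separate simulations:

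| Correlation before selection | 2,000 runs | 1,500 runs | 1,000 runs | Change (points) |
|---|---|---|---|---|
| .05 | – | 36.8 / 36.5 | 39 / 39 | about 0 |
| .3 | – | 40.3 / 40.1 | 37 / 37 | about 0 |
| .5 | 40.0 / 43.2 | 42.5 / 45.6 | 40 / 42 | 2-3 |
| .7 | 44.0 / 49.3 | 45 / 50 | 45 / 50 | 5 |
| .8 | 49.4 / 57.4 | 51 / 59 | 51 / 60 | 8-9 |

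**Effect of selection on the correlation.** Truncation point a = (2.2−2.9)/1.1 = −0.636. The inverse Mills ratio is 0.326/0.738 = 0.442. The variance factor is k = 1 + a·0.442 − 0.442² = 0.524. Among participants the correlation is r·√k/√(r²k + 1 − r²), which gives about .38-.39 for .5, .58 for .7 and .69 for .8.

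**Model B.** The correlation is set directly among participants. The underlying mean lies at the cut-off or 1 SD above it, the general decline is 0.5 or 1 SD, and the treatment effect is 0.5 SD of T0. There are four settings per correlation and 800 runs each. Control proportions are 13-38% and exercise proportions 26-58%.

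| Correlation among participants | Chi-square power | Adjusted power | Variance ratio of risk difference | AUC of T0 alone |
|---|---|---|---|---|
| .05 | 38-47% | 37-49% | 1.01 | about 0.52 |
| .3 | 39-45% | 40-50% | 0.96-0.98 | about 0.63 |
| .5 | 37-48% | 43-56% | 0.87-0.92 | 0.71-0.73 |
| .7 | 43-49% | 56-63% | 0.73-0.84 | 0.80-0.82 |

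Setting by setting, power rises by 5-8 points at .5 and by 12-18 points at .7. At .05 there is no gain.

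**Error rate under no effect.** In Model B (1,500 runs each, correlations .5 and .7) chi-square rejects 5.3% and 4.2%, and the adjusted test 5.8% and 5.8%. Model A gives about 4.5-6% for both tests. The adjusted test rejects slightly more often under no effect in Model B, so part of its power gain there may come from that; the variance ratio is the cleaner measure.

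**The case against.** The strongest reply is that nothing here is wrong. A chi-square test of a randomised 1:1 comparison keeps its error rate, and chance baseline imbalance is already allowed for in that rate. The analysis is supplementary, and covariates and intervals for such an analysis are often left to a fuller document that is not shown. This stands as to validity. It does not remove the point, because the article names the test itself rather than leaving it open.

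Three stronger readings might be inferred, and the documents do not support them.
- *That the T0 distance largely decides who crosses.* No figure in the article says so. Under Model B, T0 is a moderate predictor at a correlation of .5 and almost uninformative at the printed .05.
- *That no effect size can result.* The two-by-two counts give a risk difference or odds ratio with an interval directly; the article merely names none.
- *That the comparison is biased.* Regression to the mean is equal across arms on average under randomisation.

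It is also fair to say that a person who improves greatly from 5 without crossing is an argument against dichotomising. Logistic regression on the same binary outcome does not answer it. The RM-MANOVA on the continuous scores already captures that improvement. Finally, the analysis stays underpowered after adjustment: at correlations of .5 to .8, adjusted power under Model A is 42-60%.

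**Conclusion.** The point holds as a minor one about efficiency and reporting. The planned test is valid, but it leaves out a pre-randomisation score that partly predicts the outcome, and no effect measure is named for a comparison meant to convey clinical meaning.

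The gain ranges from nothing at low correlations to about 8-9 points of power (Model A, .8 before selection) or 12-18 points (Model B, .7 among participants). At .5, the value consistent with N = 90, it is 2-3 points if .5 is the correlation before selection (Model A) and 5-8 points if it is the correlation among participants (Model B). In the latter case the variance of the risk difference falls by 8-13%.

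All of this rests on assumed SDs, means, shifts and normal scores with 45 per arm. Hypothesis 1 and the primary RM-MANOVA are not touched.

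**What to change.** In *Analyses of primary and secondary outcomes*, replace the chi-square sentence. For each scale separately, fit a logistic regression of being below the cut-off at T6 on condition and the continuous T0 score of that same scale, and report the standardised risk difference with its 95% confidence interval. Standardising over the observed T0 scores keeps the estimate on the scale of a difference in proportions between conditions. The raw counts per arm can be shown beside it.

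The cost is one sentence of analysis wording. Both scores are already collected, and no visit, measure or participant is added. If the chi-square test is kept, naming a risk difference with its interval would still settle the reporting half of the point.

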### Analyses of weekly trajectories of employee well-being

The trajectories of employees’ weekly well-being during the intervention period will be analyzed using growth models in a multilevel modeling framework, because our weekly occasions (level 1) are nested within persons (level 2). This analyzing method allows us to estimate inter-individual as well as intra-individual patters of change over time in a powerful way [82]. The data will be analyzed using MPlus [83]. For each of the weekly indicators of employee well-being, a model will be tested. This model consists of an intercept term, and variances at the occasion and person level. Furthermore, ‘time’ (7 occasions: T0 to T6) will be added as a random factor to the model (to measure the rate of change per unit of time), as well as ‘time^2^’ (to measure a change in the rate of growth). Additionally, ‘condition’ (0 = control, 1 = exercise) will be added as a fixed factor to the model, and will interact with ‘time’, and ‘time^2^’. As such, it will be investigated whether there is an effect of exercise on the rate of change in well-being over time.

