### Weekly trajectories of employee well-being

Next to measuring the effect of exercise on these primary and secondary outcomes after the intervention period, it is also valuable to examine employees’ well-being trajectories during the intervention period. This prevents the intervention period of being a ‘black box’, in which it remains unknown which changes take place at what time. Therefore, in the current study, we will pay close attention to employee well-being during the intervention period. We will employ weekly self-administered single-item measures of fatigue, self-efficacy and sleep, which correspond to our primary and secondary outcomes. Additionally, we will investigate other single-item indicators of employee well-being, such as mood, to capture a broader range of the effects of the intervention. By doing so, we aim to provide a more fine-grained insight in how these different indicators of employee well-being develop during the intervention period, and whether weekly trajectories of these indicators differ between conditions. Although it is not possible to predict at what time these indicators change as a result from the intervention, we generally expect that:*Hypothesis 3*: during the course of the intervention period, participants in the exercise condition show a larger improvement in weekly well-being compared to participants in the control condition.

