## Discussion

This article describes the design of a two-arm RCT to evaluate the efficacy of an exercise intervention on work-related fatigue. Except for work-related fatigue, the effect of exercise on five secondary outcomes related to work-related fatigue will be studied. Furthermore, we will gain insight in how different indicators of employees’ well-being develop during the intervention period. This will inform us if, and if so, at what point in time the intervention is effective in changing these indicators. Furthermore, we also examine participants’ experiences of and the attendance to the running sessions of the exercise intervention to get a better understanding of the extent to which these experiences and activities may have differential effects on intervention efficacy.

Since we wish to investigate the effect of exercise compared to the natural course of work-related fatigue over time, and there is no standard effective intervention for work-related fatigue available yet, we choose for a wait list as control condition. To overcome possible ethical and practical concerns of wait lists in randomized controlled trials [84], we decide to employ an exercise intervention of a relatively short duration (i.e. six weeks). It could be imagined that withholding an intervention from employees with high levels of work-related fatigue for a longer period of time could worsen their problems. Furthermore, a longer waiting period for the participants in the control condition could result in higher attrition rates.

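### The article promises to show when the intervention becomes effective, but the only between-arm weekly analysis is a quadratic growth model with no onset parameter

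*Protocol article*

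**What the plan says.** The Background subsection on weekly trajectories justifies the weekly questionnaires by timing: "This prevents the intervention period of being a ‘black box’, in which it remains unknown which changes take place at what time". It also concedes that no timing can be assumed: "Although it is not possible to predict at what time these indicators change as a result from the intervention". Hypothesis 3, which follows, is about a larger improvement over the intervention period and names no week. The Discussion returns to timing and says of the weekly data: "This will inform us if, and if so, at what point in time the intervention is effective in changing these indicators".

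The analysis section specifies a multilevel growth model for each indicator. In it "time’ (7 occasions: T0 to T6) will be added as a random factor to the model", a squared term is included "to measure a change in the rate of growth", and condition "will be added as a fixed factor to the model, and will interact with ‘time’, and ‘time^2". The stated target is that "it will be investigated whether there is an effect of exercise on the rate of change in well-being over time".

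No other planned analysis compares the arms week by week. Analyses of moderators uses the same quadratic form in the exercise arm only. The post hoc tests under Analyses of primary and secondary outcomes concern T0, T6, T7 and T8, again in the exercise arm only, and do not use the weekly data.

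**The concern.** The article states a question about timing and fixes an analysis that answers a different one. The arm difference over time is described by three numbers: condition, condition by time, and condition by time squared. Together they make a parabola, which has no parameter for when an effect begins. Its height in any week is set by all seven occasions together. Because condition enters freely, the curve need not be zero at T0, before any running session.

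If the fitted curves were used to support the Discussion sentence, the start, peak or fading of the effect could be reported in the wrong week. The test of Hypothesis 3 is not at stake; the timing statement is.

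**Working it through.** The article gives no numerical figure for the weekly analysis, so there is none to reproduce. The check asks what the specified curve shows when the true weekly arm differences are known.

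**Inputs.** Seven occasions, t = 0 to 6, and an arm difference modelled by 1, t and t² (both from the analysis section). The true patterns below are assumptions, with the full effect set to 1 and no noise.

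**Formula.** For equally spaced occasions, use the orthogonal contrasts L = (−3, −2, −1, 0, 1, 2, 3), sum of squares 28, and Q = (5, 0, −3, −4, −3, 0, 5), sum of squares 84. The fitted difference is mean(d) + L·(ΣLd/28) + Q·(ΣQd/84). With complete data and random intercept, time and time², generalised least squares gives the same fitted values.

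**Abrupt start at T4**, d = (0, 0, 0, 0, 1, 1, 1):
- mean = 3/7 = 0.429; linear = 6/28 = 0.214; quadratic = 2/84 = 0.024.
- At T3: 0.429 + 0 − 4 × 0.0238 = 0.33, where the truth is 0.
- At T4: 0.429 + 0.214 − 3 × 0.0238 = 0.57, where the truth is 1.
- All weeks: −0.10, 0.00, 0.14, 0.33, 0.57, 0.86, 1.19.

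**Immediate, constant effect from T1**, d = (0, 1, 1, 1, 1, 1, 1):
- mean = 6/7 = 0.857; linear = 3/28 = 0.107; quadratic = −5/84 = −0.060.
- At T0: 0.857 − 3 × 0.107 − 5 × 0.0595 = 0.24, where the truth is 0.
- All weeks: 0.24, 0.64, 0.93, 1.10, 1.14, 1.07, 0.88. This shows a peak at T4 and a later decline, neither of which exists.

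**Week just before a delayed abrupt start:**

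| True start | Week before | Fitted there (truth 0) |
|---|---|---|
| T2 | T1 | 0.36 |
| T3 | T2 | 0.43 |
| T4 | T3 | 0.33 |
| T5 | T4 | 0.29 |
| T6 | T5 | 0.36 |

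**Gradual courses**, scaled to 1 at T6, largest error in any week:
- linear gain: 0.00;
- saturating gain, time constant 2 to 4 weeks: 0.04 to 0.01;
- S-shaped (logistic) gain, midpoint week 2 to 4: 0.06 to 0.07;
- linear ramp beginning after T1, T2 or T3: 0.07 to 0.10.

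**Effect on inference.** Simulation of 4,000 trials with assumptions not in the article: 45 per arm, SD 1, within-person correlation 0.5. The table gives the share of trials in which change from T0 differs significantly between arms (two-sided 5%, unadjusted), for a true abrupt start of 0.5 SD at T4.

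| Model | T1 | T2 | T3 | T4 | T5 | T6 |
|---|---|---|---|---|---|---|
| Quadratic | 7.7% | 12.6% | 22.8% | 48% | 83% | 97% |
| Free weekly means | 5.0% | 5.2% | 4.5% | 67% | 65% | 66% |

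With 0.8 SD, the quadratic is significant at T3 in 52% of trials, although nothing has happened by then. With no effect in any week, both approaches reject at about 5%. In the 0.5 SD scenario the joint test of the two condition-by-time terms has about 94% power, so the model serves Hypothesis 3 well.

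**The case against.** The best defence has four parts.

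**The model matches its hypothesis.** Hypothesis 3 is about improvement over the period, and the analysis section claims no more than an effect on rate of change. This stands. A reader might infer that the weekly analysis is invalid; the documents do not support that, and the null error rate and power above point the other way.

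**Abrupt jumps are unfavourable to a quadratic.** The running schedule builds up gradually, so the benefit may too, and for smooth courses the fitted curve follows the weekly differences closely. This also stands. A reader might infer that the model always shows effects in weeks that have none; that is too strong. But the article itself says the timing cannot be predicted, and a gradual training load does not guarantee a gradual response, so a smooth course cannot be taken for granted.

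**The timing claim is one descriptive sentence, and nothing says the curves will be read as an onset week.** It is true that no such reading is announced, and a fitted difference with its confidence band does say something about where the curves separate. But the week of separation depends on the imposed shape and on power. Timing is also given in the Background as a reason for collecting the weekly data, so it is more than a stray remark.

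**Week-specific contrasts have modest power here, and a condensed article may leave supplementary models to an analysis plan.** The power limit is real and shapes the fix. The second part does not remove the point: it concerns a mismatch between two statements in the article, not a missing detail.

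**Conclusion.** The point holds in a limited form. The article says the weekly data will show when the intervention is effective, and no planned between-arm analysis answers that. The quadratic model is sound for Hypothesis 3 and should stay.

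The distortion in timing is conditional. It is 29 to 43% of the full effect in the week before a delayed abrupt start, 24% at T0 for an immediate constant effect, and nil to about 10% for linear or gradual courses. These figures assume complete data and the stated true patterns. The rejection rates rest further on the assumed 45 per arm, SD 1 and correlation 0.5. The weekly indicators are neither primary nor secondary outcomes, so the trial's main conclusion is untouched. The mismatch should still be corrected, because the remedy uses data already being collected.

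**What to change.** Keep the quadratic growth model as the test of Hypothesis 3. For each weekly indicator, add a supplementary multilevel model with occasion as a seven-level factor and the arms constrained equal at T0. The constraint is justified because Randomization and blinding places randomisation after the baseline measurement. Report the arm difference with its 95% CI at each of T1 to T6.

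For any claim about a particular week, state a multiplicity adjustment over the six weeks, for example Holm. Without one, six independent tests at 5% would carry a familywise error of 1 − 0.95⁶, about 26%. A rule that works backwards from T6 is less suitable, because it cannot credit an early benefit that has faded by then. Describe timing statements as exploratory, and say that a non-significant week is not evidence of no effect.

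The alternative is to restrict the Discussion sentence to differences in the rate and shape of change, and to soften the Background rationale to match.

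The cost is one extra model per indicator, wider weekly intervals and limited power to date an effect. Under the same assumptions (0.5 SD, 45 per arm, correlation 0.5), the standard error of a weekly difference with equal arms at T0 is √(0.75 × 2/45) = 0.183, so the expected z is 0.5/0.183 = 2.74. Power in one week is then about 78% unadjusted (critical value 1.96) and about 54% at the strictest Holm step (0.05/6, critical value 2.64).
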